### Study population

The target population includes individuals aged 18 years and above who seek care for NCDs. The study population shall be the healthcare workers of all cadres across healthcare facilities at various levels of healthcare delivery (including Ayushman Arogya Mandirs, sub-centers, PHCs, CHCs, district hospitals, and tertiary care hospitals)

### Eligibility criteria

#### Inclusion criteria.

The healthcare workers aged 18 years and above, of all cadres across healthcare facilities involved with NCD and Mental Health at various levels of healthcare delivery (including sub-centers, AAMs, PHCs, CHCs, district hospitals, and tertiary care hospitals) in the selected districts across the seven states, interested in participating in the study and willing to provide consent for the same, shall be eligible for inclusion in the study.

#### Exclusion criteria.

Those refusing to consent or not interested in participating in the study.

### Sample size

One district from each of the seven states shall be included in the study. In each district, blocks (rural areas) and wards (urban areas) shall be listed. A listing of healthcare facilities across each of the districts shall be carried out.

The study shall be carried out in three phases: Phase I (Formative research), Phase II (Model Optimization [Mx]), and Phase III (Full implementation and evaluation).

For **Phase I**, one block or ward from each of the districts shall be included. All the health facilities (including AAMs, sub-centers, PHCs, CHCs, district hospitals, and tertiary care hospitals) in the selected block or ward shall be included. Each block and ward are expected to have one CHC and three to six PHCs. Each PHC is expected to have 5–6 AAMs. The district hospital in each of the districts shall also be included in this phase of the study. A service delivery Model 0 will be developed in collaboration with the key stakeholders, co-development of the implementation model, and the co-developed Model 0 will then be implemented in one block.

In **Phase II**, the implementation model will be refined in the block or the ward based on the challenges and feedback from all the stakeholders. The study will follow an iterative process until the optimized version of the Model Mx is achieved.

In **Phase III**, the final model shall be implemented across the district at each of the sites. The primary evaluation outcome is facility-level coverage of the mental health screening and management strategy. We require an estimate of coverage of 70% with an absolute precision of ±10% and 95% confidence. Using the single-proportion formula n = Z^2^ p (1 − p)/ d^2^, with Z = 1.96, p = 0.70, and d = 0.10, gives n = 80.7, rounded up to 81 health facilities per district. The implementation cascade was designed such that screening, referral, and management rates of ≈90% at each step yield an overall coverage of 0.9 × 0.9 × 0.9 = 0.729 (≈72.9%), which is slightly conservative with respect to the 70% target. Because the primary unit of analysis is the facility, this sample-size calculation does not require an intra-cluster correlation correction; however, if analyses are to be performed at the individual level or if clustering is a concern, the sample will be inflated by an appropriate design effect (DEFF = 1+ (m − 1) ρ), and allowance will be made for anticipated non-response. A sensitivity analysis using DEFF values between 1.2 and 1.5 and a 10% non-response adjustment is presented in Supporting Information S1 Table. (S1 Table – Sensitivity Table using Appropriate Design Effect)

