**Feasibility (Yes/No)** (compatible or actual fit) The extent to which an intervention can be carried out in a particular setting or organization	Facility and Individual providers Organization or setting	• Quantitative assessments from the Healthcare facility registers and government databases.	• Proportion of patients screened for MSUD among those screened/confirmed with NCD (N + M) • Proportion of screened positive/confirmed for MSUD managed, are under follow up, complied with referral
**Fidelity** The degree to which an intervention was implemented as it was designed in an original protocol, plan, or policy	Facility and Individual provider (adherence, quality of delivery, program component differentiation, exposure to the intervention, and participant responsiveness or involvement)	• Quantitative assessments from the Health care facility registers and government databases.	• Proportion of facilities who started integrating the model • The proportion of patients who initiated the treatment, following up with the health facility • The proportion of the patients in whom the continuum of care was ensured.
**Penetration** (integration of a practice within a service setting and its subsystems)	Organization or setting Facility level: The integration of MH screening in NCD within public health system; (the extent to which MH screening, linkages and treatment completed)	• Quantitative assessments from the Health care facility registers and government databases.	• Proportion of NCD patients screened for MSUD ◦ numerator assessed with patients registered in the digital App/ record review ◦ denominator assessed with HWC/PHC/CHC register (patients with NCD registered at the facility) • Among those with a positive MSUD screen ◦ proportion who are screened, managed and referred ◦ numerator assessed with patients registered in the digital App/ record review ◦ denominator assessed with HWC/PHC/CHC register (patients with NCD registered at the facility)

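### The ±10% precision behind 81 facilities per district belongs to a facility yes/no result, while all three primary outcomes are proportions of individuals

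*Protocol article*

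**What the plan says.** In the Protocol article, Sample size, the Phase III text names its target: "The primary evaluation outcome is facility-level coverage of the mental health screening and management strategy". It then sets the requirement: "We require an estimate of coverage of 70% with an absolute precision of ±10% and 95% confidence". The single-proportion formula, "with Z = 1.96, p = 0.70, and d = 0.10, gives n = 80.7, rounded up to 81 health facilities per district", fixes the number. The 70% is set beside a cascade in which "screening, referral, and management rates of ≈90% at each step yield an overall coverage of 0.9 × 0.9 × 0.9 = 0.729".

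On clustering, the text says: "Because the primary unit of analysis is the facility, this sample-size calculation does not require an intra-cluster correlation correction". After a semicolon the same sentence continues: "if analyses are to be performed at the individual level or if clustering is a concern, the sample will be inflated by an appropriate design". The inflation factor meant there is DEFF = 1 + (m − 1)ρ, with an allowance for non-response. A sensitivity table with DEFF 1.2 to 1.5 and 10% non-response is cited (S1 Table, not shown). No value of m or ρ appears in the text.

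Primary outcomes lists three proportions, each with people in the denominator: NCD attenders who are screened, screen-positives who are linked to services, and linked persons who start treatment. A facility proportion, "Proportion of facilities who started integrating the model", is listed under Secondary outcomes and again in Table 7. Study setting fixes 567 facilities in total and says they serve the patient outcome as well as the implementation and service outcomes.

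**The concern.** The term p(1 − p) divided by a number of facilities is the variance of a facility-level 0/1 result. No primary outcome has that form, and no rule says when a facility counts as covered. The phrase facility-level coverage does not supply one. Table 7 measures penetration as patients in the app or records over NCD patients on the facility register, which gives a continuous ratio for each facility.

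The ±10% at 95% confidence is the precision statement offered for the main aim of at least 70% coverage, and it does not describe the outcomes that will be reported against that aim. The clustering text is also not carried through. The condition for a design effect is met by the primary outcomes, but 567 is the uninflated number. If the no-ICC statement were read across to the analysis, patient-level confidence intervals could be computed as though patients within a facility were independent, and they would be too narrow.

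**Working it through.** **1. The plan's own figure.** Inputs from Sample size: Z = 1.96, p = 0.70, d = 0.10.

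- n = 1.96² × 0.70 × 0.30 / 0.10² = 80.67, rounded up to 81. Over seven districts, 7 × 81 = 567. Both reproduce.
- Half-width at n = 81: 1.96 × √(0.21/81) = 0.0998, or ±9.98 points, for independent facility yes/no results.

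**2. Patient-level proportion, equal-sized facilities.** Half-width = 1.96 × √(0.21 × [1 + (m − 1)ρ] / (81m)), where m is patients per facility. The document gives neither m nor ρ, so these are assumptions, with p held at 0.70.

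| m | ρ = 0.01 | ρ = 0.05 | ρ = 0.20 | ρ = 0.30 |
|---|---|---|---|---|
| 20 | ±2.4 | ±3.1 | ±4.9 | ±5.8 |
| 50 | ±1.7 | ±2.6 | ±4.6 | ±5.6 |
| 100 | ±1.4 | ±2.4 | ±4.6 | ±5.5 |

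For m above 1, the value ±9.98 is reached only at ρ = 1, when every patient in a facility has the same result.

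**3. Mean of facility coverages.** Half-width = 1.96 × SD/√81. With an assumed between-facility SD of 0.10 to 0.30 this is ±2.2 to ±6.5 points. Reaching ±10 needs an SD of about 0.458 = √0.21, the largest possible at a mean of 0.70.

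**4. Unequal facility sizes.** DEFF = 1 + ([1 + CV²]m − 1)ρ. The planned facilities run from sub-centres to tertiary hospitals, so variation is likely, but no CV is given. At assumed m = 50 and ρ = 0.2:

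- CV 1: DEFF 20.8, ±6.4 points
- CV 2: DEFF 50.8, ±10.1 points
- CV 3: DEFF 100.8, ±14.2 points

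**5. Shrinking denominators (second and third outcomes).** Take 20 NCD attenders per facility, 90% screened and 10% screen-positive (the first and last are assumptions): 20 × 0.9 × 0.1 = 1.8 screen-positives per facility. At ρ = 0.1, 1.96 × √(0.21 × 1.08/145.8) gives ±7.7 points. With equal sizes, ±10 is passed only below about 81 such patients in a district, that is, fewer than one per facility.

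**6. The promised design effect.** Multiplying 81 by 1.2 gives 97.2, so 98 facilities; by 1.5 gives 121.5, so 122. Over seven districts that is 686 to 854, against 567 planned. Applying it this way would not repair the calculation in any case. With m as patients per facility, 1 + (m − 1)ρ inflates a number of patients, whereas 81 is a number of clusters.

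**7. Cost of ignoring clustering in the analysis.** At assumed m = 100 and ρ = 0.05, DEFF = 1 + 99 × 0.05 = 5.95. An unclustered interval would be too narrow by a factor of √5.95 = 2.4.

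**The case against.** The best defence is that the clustering sentence has a second half. The protocol does not rule out an ICC correction altogether; it commits to one if analysis is at the individual level. That stands, and it is wrong to say that the plan ignores clustering. It does not remove the problem, because the stated condition is met by the listed primary outcomes and the number of facilities was not changed.

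A second defence is that precision for each outcome and ICC values can be left to a fuller document. That is fair for the detail. The point here is narrower: the article attaches a stated precision to outcomes it does not fit.

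Several stronger readings are tempting and are not supported:

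- **The 70% was derived from the cascade.** The text enters 0.70 as the target; the product is 0.729 and is only compared with it.
- **The integration outcome is the only facility yes/no measure.** Table 7 lists others, such as facilities where screening is done and facilities that continue the model.
- **Nesting makes the facility yes/no precision worse than ±10.** The text says "Each PHC is expected to have 5–6 AAMs", but in describing Phase I blocks. Nothing says that Phase III samples whole PHC clusters, and under simple random sampling of facilities within a district nesting would not inflate the variance.
- **DEFF 1.2 to 1.5 is implausibly low.** That depends on what m counts, which the text does not say, and S1 Table is not shown.

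**Conclusion.** The mismatch holds. The arithmetic is correct, but ±9.98 points is the precision of an independent facility yes/no result at p = 0.70. It is not the precision of any of the three primary outcomes, nor of a mean of facility coverages. The protocol also does not reconcile its own conditional design effect with the 567 facilities it fixes.

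A reader might infer that 81 facilities per district are too few. The documents do not show this. With equal-sized facilities the assumed ranges give about ±1.4 to ±5.8 points for a patient-level proportion, and ±2.2 to ±6.5 for mean facility coverage, all tighter than ±10. Precision worse than ±10 arises only with very unequal sizes (±14.2 at m = 50, ρ = 0.2, CV 3) or very few screen-positive or linked patients. All these figures rest on assumed m, ρ, CV and SD, because the document gives none of them. What is established is that the stated precision is attached to the wrong quantity, not that the study lacks precision.

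**What to change.** - Keep 81 facilities per district.
- Make Sample size and Primary outcomes name the same unit of analysis. If mean facility coverage is the intended estimand, say so and base precision on a between-facility SD.
- Remove the statement that no ICC correction is needed, as far as it concerns the patient-level primary outcomes, and settle the conditional design-effect clause against the 567 facilities in Study setting. Define m.
- Replace the single ±10% with the expected 95% precision for each of the three primary outcomes, using the facility as cluster, expected denominators (NCD attenders, screen-positives, linked persons), an ICC range and facility-size variation.
- State that these outcomes will be reported with facility-clustered confidence intervals.
- Keep the current formula only for facility yes/no outcomes, and say that it assumes independent facilities.

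The cost is protocol wording and one recalculated table, with no added facilities. Some stated precisions may become less favourable, most likely for the second and third primary outcomes.

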### Sampling method

We will be using a multistage sampling approach that will be adopted to ensure representation across multiple stakeholder groups and healthcare delivery levels. Initially, the seven states were selected by the expression of interest, and later districts were selected after the discussions with the respective states.

In **Phase 1**, purposive sampling will be used to recruit key informants, including policymakers, administrators, healthcare workers, community representatives, and patients, to capture diverse perspectives on mental health integration.

In **Phase 2** and **Phase 3**, all healthcare facilities—Ayushman Arogya Mandirs (AAMs), Sub-centres (SCs), Primary Health Centres (PHCs), Community Health Centres (CHCs), and District Hospitals (DH)—as well as all health cadres involved in mental health service delivery under the District Mental Health Programme (DMHP), including Medical Officers (MOs), Community Health Officers (CHOs), and Accredited Social Health Activists (ASHAs), will be included.

This staged approach allows for systematic recruitment from broader administrative and policy levels down to frontline providers and end-users, facilitating comprehensive data collection across the health system. A flowchart of the multistage sampling method is presented in Fig 1.

**Fig 1 pone.0332359.g001:**
[figure not shown]
Flow chart of multiphase sampling of ICMR MINDS.

### Intervention components

The intervention components of the research study include tools for integrated screening and assessment for mental health conditions; treatment guidelines, workflows, and pathways that integrate mental health interventions within NCD care; the development of a digital platform/app; training for healthcare providers on integrated care practices; and patient education and engagement to raise awareness and promote shared decision-making.

(1) Tools for integrated screening and assessment for mental health conditions shall be developed for all levels of healthcare personnel. These shall include the screening tools to be used by Accredited Social Health Activists (ASHA) and Community Health Officers (CHOs) and assessment tools to be used by the Medical Officers (MO). The screening tools shall be developed by the ICMR HQ in consultation with mental health experts. The assessment tools for the MOs shall be developed by the participating sites. These screening and assessment tools shall be developed for emergency mental health conditions, common mental disorders (depressive disorder and anxiety disorder), substance use disorder (tobacco and alcohol use disorder), and self-harm. The proposed screening tool shall be based on the mhGAP intervention guide (by the World Health Organization), Patient Health Questionnaire-9 (PHQ-9) [22], and the Generalized Anxiety Disorder-7 (GAD-7) [23] and shall include a screener for tobacco, alcohol, and other psychoactive substances [24], which will be translated to local languages in each state and validated before using it. The PHQ-9 and GAD-7 are validated scales and available in local languages. The assessment tools shall be based on the recent version of the diagnostic system, viz., International Classification of Diseases (ICD)-11. All the tools will be administered in an interview format.(2) The workflows and pathways that integrate mental health interventions within NCD care shall be developed. These shall be developed by the ICMR HQ and the study sites. These shall be based on the WHO mhGAP intervention guide [25] and other guidelines on the management of MSUDs. In order to ensure the applicability to the local context, the recommendations made by various organizations, associations, and departments in the county shall be taken into consideration. The ICMR Standard Treatment Workflow of India for Psychiatry [26] and the ICMR Community Health Officers’ Mental Health Workflow shall be some of the resources (S1 Fig). Drug interactions shall be considered while drawing up a management plan. Screening, assessment (diagnosis and severity of the disorder), and management (treatment and referral) shall constitute the intervention package. All aspects of the intervention package shall be translated into the local languages.(3) A digital platform and smartphone app shall be developed. These shall be developed for various purposes, including the digitization of the screening tools, referral and management protocols using an electronic decision support system; tracking of the number of participants screened, treatment initiated in screen positives, number of follow-ups by the participants, number of participants linked to CHC, District, and Hospitals; care coordination mechanisms for effective communication and referral systems using recall and reminder systems; and monitoring and evaluation of the project.

A mHealth App Usability Questionnaire (MAUQ) will be used for assessing the usability of these applications. The MAUQ evaluates mHealth app usability using a set of targeted questions across three main categories, including Ease of Use and Learnability, Interface and User Satisfaction, and Usefulness. The provider version of the questionnaire shall be used for the purpose of the study. The correlation coefficients among the MAUQ, Post-Study System Usability Questionnaire (PSSUQ), and System Usability Scale (SUS) were found to be high [27].

(4) Trainings shall be carried out for the healthcare providers on integrated care practices. Health care professionals across different cadres (including ASHAs, CHOs, Nurses, and MOs) will receive training. The trainings shall be focused on screening and assessment tools, treatment and referral flow, and use of digital platforms/apps. The training shall include the induction training in the beginning, followed by mentoring and ongoing supportive supervision. Cascade trainings shall be carried out based on the modules developed as part of the project.(5) Content aimed at patient education and engagement to raise awareness and promote shared decision-making shall also be developed and disseminated to the community through an awareness programme.

The key intervention components that shall be delivered at different levels of the health system are provided in Table 1.

**Table 1 pone.0332359.t001:** Key intervention components that shall be delivered at different levels of the health system.

	Subcenter/AAM	PHC	CHC	DH/MC
Screening	+	+	+	–
Diagnosis	–	+	+	+
Treatment	–	+	+	+
Linkage	+	+	+	–
Training of health care providers	+	+	+	+
Use of Digital platform/ App	+	+	+	+
Patient education and engagement	+	+	+	+

**Abbreviations:** AAM-Ayushman Arogya Mandir; PHC-Primary Health Center; CHC-Community Health Center; DH-District Hospital; MC-Medical College.

The health care providers across these settings shall include ANM, CHO, MO, nurses-PHC, and CHC doctors and nurses.

### Status and timeline of the study

The study has been sanctioned for the duration of three years, from 01.02.2024 to 31.01.2027.

**A) Recruitment and Data Collection**

Recruitment Initiation: Participant recruitment commenced in May 2025 and is ongoing.Participant Enrollment Completion: The target number of participants is expected to be enrolled by October 2026.

**B) Data Collection Completion:** Data collection is anticipated to conclude by October 2026.

**C) Results Availability:** Preliminary results are projected to be available by February 2026. The final results will be ready after two years, i.e., January 2027.

### Phases of Study Implementation

This research will comprise three phases of implementation: Phase 1—Formative Research, Phase 2—Model Optimization, and Phase 3—Full Implementation and Evaluation. The spirit figure of the phases of ICMR MINDS is provided in Fig 2.

**Fig 2 pone.0332359.g002:**
[figure not shown]
Spirit Figure of Phases of ICMR MINDS.

#### Phase-1-Formative Research.

The formative research phase aims to assess the service availability and health system readiness in terms of infrastructure. It will attempt to identify key facilitators and barriers to integrating mental and substance use disorder (MSUD) care into the broader non-communicable diseases (NCD) framework. This phase involves a comprehensive situational analysis, including desk reviews, SWOT analysis, and stakeholder interviews, which will inform the development and optimization of the intervention model [28–31]. The details of the overview of the situational analysis are presented in Fig 3.

**Fig 3 pone.0332359.g003:**
[figure not shown]
Overview of Situational Analysis.

1. ***Desk Review*:** Desk review will be used for identification of potential facilitators and barriers to integration of care of mental disorders and substance use disorders into care for other NCDs. Multiple resources from Government and other websites will be explored to gather information regarding the same. Information on the domains of prevalence, mortality, morbidity, risk factors, economic burden, care gap, digital intervention, knowledge, attitude & practices related to common NCDs and mental health conditions, governance, human, physical, and intellectual resources, health financing and information, health insurance, and effectiveness of m-health and telemedicine for access to NCD care and mental health care will be collected from various resources.2. ***SWOT Analysis and Pathways to Care Mapping***: Using insights from the desk review and state-level mental health and NCD indicators, we will perform a SWOT (strengths, weaknesses, opportunities, and threats) analysis. This analysis will help identify site-specific advantages and limitations concerning the integration of MSUD and NCD care. Pathways to care mapping will complement the SWOT analysis by visually representing the current care journey for patients with MSUD and NCDs within each healthcare facility. This mapping exercise will highlight potential bottlenecks, missed opportunities for early intervention, and referral gaps, thereby informing the design of an optimized care pathway within the proposed model.3. ***Stakeholder Interviews:*** To gain a comprehensive perspective, stakeholder interviews will be conducted through in-depth interviews (IDIs) and focus group discussions (FGDs) with various participants, including patients, healthcare workers, administrators, and policymakers. The IDIs and FGDs will explore stakeholders’ perceptions of the current system, their expectations for integrated MSUD and NCD services, and perceived challenges and benefits of the new model.

**(a) Focus Group Discussions (FGDs):** A specific guide will be developed for conducting the FGDs of participants. The principle of data saturation will be followed to guide the number of FGDs required at the selected sites. A minimum of four FGDs will be conducted in each of the seven districts. These shall include two FGDs for patients/service users and two for healthcare providers, including CHOs and ASHAs.

**(b) In-Depth Interviews (IDIs):** A specific interview guide will be developed for conducting the IDIs of participants. The principle of data saturation will be used. We will be conducting the IDIs of patients/service users, Health Care Workers (ASHAs, nurses, CHOs, MOs, Psychologists, Psychiatrists and other specialist physicians), health administrators, program managers and policymakers such as Civil surgeon, Chief Medical Officer (CMO), Medical officer In- charge (MOIC) CHCs & PHCs, program manager of National Programme- Non Communicable Diseases (NP-NCD), District Mental Health Program (DMHP)/ National Mental Health Program (NMHP), National Tobacco Control Program (NTCP), District/Block program manager, NGO staff such as that of WHO/NCD Alliance/Voluntary Health Association and local NGOs, members of Alcoholics Anonymous, state-level nodal officers and program officers of NCD, and mental health-related programmes.

**4. *Situational analysis write-up:*** The initial SWOT analysis and care pathways map collected during the desk-based review and the interviews will form the situational analysis. This phase shall be of particular use for the identification of potential barriers and facilitators for the implementation of the model. We will be using the Consolidated Framework for Implementation Research (CFIR) to identify the determinants of why the baseline rates of screening, assessments, and management are low [32]. The details of the domains and constructs for the ICMR MINDS based on CFIR are provided in Table 2.

**Table 2 pone.0332359.t002:** List of the five domains and underlying constructs according to the Consolidated Framework for Implementation Research (CFIR).

Intervention Characteristics	Refers to characteristics of the intervention.	• Screening with PHQ-9 (depression), GAD-7 (anxiety), alcohol use screener (alcohol) and tobacco use screener (tobacco) • WHO mhGAP Intervention guide • ICMR standard treatment workflow **•** Cost of delivering the intervention (time, opportunity cost)
Individual Characteristics	Refers to characteristics of the individuals who would be key for implementation of an intervention, which include the program managers, health care providers and end users	• Providers • Knowledge and motivation of HCWs for screening and treatment • Training and capacity building of HCWs • Beneficiary • Socio economic status • Family dynamics • Empowerment • Age, sex
Outer settings	Refers to the economic, political, social, and cultural context which would influence implementation of the intervention	**•** Politico-economic context
Inner settings	Refers to the health system, and health facility, context which would influence implementation of the intervention.	• Infrastructure • Human resources • Essential medicine supply
Process	Focuses on engaging the relevant stakeholders, executing, reflecting, and evaluating with the aim of optimizing the implementation model for the intervention	**•** Stakeholder Engagement

***Stakeholder Workshop for Co-Development*:** Following the situational analysis, co-development workshop will be organized with all key stakeholders, including site investigators, healthcare providers, state health officials, and representatives from ICMR headquarters. During this workshop, findings from the formative research will be discussed in detail, allowing for collaborative decision-making on intervention priorities, care pathways, and service delivery strategies. Through a series of interactive sessions with the stakeholders, Model 0 (M0) will be developed, incorporating their insights to ensure alignment with local contexts and health priorities.

The designing, piloting, and refining of the implementation model (M0) for integrating MSUD care into NCD services will be done. This model will be based on findings from the formative research phase, targeting optimal workflows and interventions for screening, assessment, management, and referral of MSUDs within NCD care pathways. The model development will follow an iterative process with continuous feedback loops to optimize the intervention for effective, scalable implementation (Table 1). Key components of this phase include:

